### Duration of treatment period and follow-up

In the both the clinical and public pilots, patients will be recruited for a period of 7 months, and treated and followed up for 6 months.

### Measures: baseline and outcome and process measures

The clinical pilot and public pilot are different interventions with shared metrics and also exclusive ones to each case. The primary outcome, the smoking cessation rates, will be measured at the 60, 120, and 180-day follow-up time points, using the urinary cotinine and expired carbon monoxide levels in the clinical pilot case, and the self-reported questionnaires in the public pilot case. To assess the secondary outcomes, different metrics are required. Table 2 includes information about how they will be calculated, to which other metrics they will be compared, and to which pilot they are related.

**Table 2 Tab2:** Description of metrics to assess the primary and secondary outcome

Metric	Calculation	Comparisons	Pilot	Related secondary outcome
Primary outcome				
Smoking cessation rate	Total number of people who relapsed / total number of people in the group at 60 days, 120 days, and 180 days of their quitting date	• User engagement at an individual level • User engagement at an aggregated level • User mobile app usage • User quitting attempts • User lifestyle feedback • Physical activity	• Clinical • Public	System influence on smoking cessation and app influence on users physical activity levels
Secondary outcomes				
User engagement at an individual level	Messages read by the user / total number of messages sent to the user	• Smoking cessation rate	• Public • Clinical	System influence on smoking cessation
Engagement at an aggregated level	Mobile application rolling retention, session length distribution, session frequency, sessions per user, return rate	• Smoking cessation rate	• Public • Clinical	System influence on. smoking cessation.
User quitting attempts	Number and date of quitting attempts	• Smoking cessation rate	• Public • Clinical	System influence on smoking cessation
User app behavior	Time spent per app section	• User message ratings • User satisfaction with messages	• Public • Clinical	App usage. and opinions on messages the users received
User satisfaction with messages	Satisfaction questionnaire	• User mobile app usage • Mobile app behavior • User message ratings	• Clinical	App usage and opinions on messages the users received
User message ratings	Users’ votes for each message on a 5-star scale	• User app behavior	• Public • Clinical	App usage and opinions on messages the users received
User lifestyle feedback	Comparison of changes in user lifestyle (at baseline and after 6 months) through the questionnaires: EQ-5D-5 L, IPAQ for physical activity, and SF-36	• Smoking cessation rate • Mobile app usage	• Clinical	App influence on users physical activity levels
Physical activity	Total time (min) of activity per user, retrieved by GoogleFit	• Smoking cessation rate • Mobile app usage	• Public • Clinical	App influence on users physical activity levels

*EQ-5D-5 L* EuroQol 5-dimension 5-level questionnaire, *IPAQ* International Physical Activity Questionnaire, *SF-36* Short Form 36-item Health Survey

Although they are not necessary to the assessment of the primary and secondary outcomes, the metrics described in Table 3 will also be retrieved and analyzed because they are considered relevant and potentially useful.

**Table 3 Tab3:** Description of additional metrics to be measured in the study

Metric	Calculation	Pilot
User reliability	Comparison of the abstinence self-report at 2-week intervals with the measurements of the CO-oximeter	Clinical
QALY (financial aspects)	Healthcare resource utilization and cost analysis (cost of devices used, pharmacological treatment and time spent for various purposes)	Clinical
Precision of the recommender system	Messages sent and rated more than four stars / total number of rated messages	Public Clinical
Smoke-free period	Time range between quitting date and the last smoke-free report	Clinical

*CO* carbon monoxide, *QALY* quality-adjusted life year

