## Methods

### Design and setting

The primary objective of this study is to assess whether tailored motivational messages supporting smoking cessation—as selected by a health recommender system and delivered by mobile phones to patients—contribute to higher smoking cessation rates.

Secondary objectives include: (1) comparing smoking cessation rates to other user metrics and technical aspects of the system; (2) investigating the relationship between usage of the app used in the 3M4Chan intervention [35] and users’ opinions of messages; and (3) determining if a relation exists between the users’ physical activity levels and their mobile app usage, and their smoking cessation rates.

Both the primary objective and the secondary objectives are common for the clinical and public pilots, although their methodologies and assessments do not completely coincide.

The present document shows the protocol version 1.0.4, 30 May 2018. Major protocol amendments, if any, will be handled by the Taipei Medical University informing any involved stakeholder, and updating the ClinicalTrials.gov registry diligently. Table 1 describes the clincal and public pilot. We followed the Standard Protocol Items: Recommendations for Intervention trials (SPIRIT) guidelines while writing this protocol manuscript (see Additional file 1).

**Table 1 Tab1:** Description of the clinical and public pilot

Name of the pilot	Number of patients	Groups	Treatment	Data to be assessed
Clinical pilot (RCT; 100 patients)	50	Control	Usual care (behavioral therapy and pharmacological treatment)	Smoking cessation rate (clinically validated)
	50	Intervention	Usual care + 3M4Chan app (advanced tailored messages)	Smoking cessation rate (clinically validated)
				Recommender system
				User engagement
				Physical activity
Public pilot (RCT; 1000 patients)	500	Control	m-health (basic tailored messages)	Smoking cessation rate (self-reported)
				Recommender system
				User engagement
				Physical activity
	500	Intervention	m-health (advanced tailored messages)	Smoking cessation rate (self-reported)
				Recommender system
				User engagement
				Physical activity

*RCT* randomized controlled trial

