### Statistical analysis

In the clinical pilot, patients will be classified as either smokers or non-smokers according to their positive or negative values in the urine test and the expired CO tests (PiCO values between 0 and 6 will be considered non-smokers) at each follow-up visit. In case of discrepancy between tests, we will consider the patient as a smoker. We will perform repeated analysis of variance (ANOVA), and provide *p* values, to compare the number of non-smokers in the intervention versus control group at 2 months, 4 months and 6 months of their quitting day.

In the public pilot, users will be considered to be non-smokers according to their self-reported answer to the question: “Are you still resisting the temptation or have you smoked? Please, be honest.” We will perform repeated ANOVA, and provide *p* values, to compare the number of non-smokers in the intervention versus control group every 2 weeks.

For secondary outcomes, the numerical variables (user engagement at aggregated level, user mobile app usage, user quitting attempt, user app behavior, and user lifestyle feedback EuroQoL 5 dimensions 5 levels questionnaire (EQ-5D-5 L) and Short Form 36-item Health Survey (SF-36), and physical activity) will be assessed with *T* tests and variance ANOVA tests. Categorical variables (user engagement at individual level, user satisfaction with messages, user message ratings, and lifestyle answers to the International Physical Activity Questionnaire (IPAQ)) will be assessed with chi-square tests. In addition, we intend to study the combination of all metrics with a linear regression analysis, and the Kaplan-Meier method to analyze the overall survival rate (non-smokers). All tests will be two-tailed and with a significance level set at 0.05. All analyses will be done according the intention-to-treat principle, and using the SPSS software version 25. Missing data will be calculated with the last observation carried forward.

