### Problems anticipated

The dropout rate among participants is one of the main challenges we anticipate for this study. Patients might dropout by ceasing to share EHR data, by terminating their use of the app, or by becoming unresponsive to follow-ups over the course of the trial.

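### Table 2 relates cessation to app engagement with no cut-off before the outcome, so relapse can itself create the association labelled as system influence

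*Protocol article*

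**What the plan says.** The first secondary objective (Design and setting) is "comparing smoking cessation rates to other user metrics and technical aspects of the system". Table 2 (Measures: baseline and outcome and process measures) puts this into practice:

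- Individual engagement is "Messages read by the user / total number of messages sent to the user".
- Aggregated engagement is "Mobile application rolling retention, session length distribution, session frequency, sessions per user, return rate".
- Both are compared with the smoking cessation rate, and both are filed under "System influence on smoking cessation".

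Cessation "will be measured at the 60, 120, and 180-day follow-up time points". In both pilots patients are "treated and followed up for 6 months", so app exposure and outcome share one window. For the analysis, the Statistical analysis section names t tests, ANOVA and chi-square tests, and adds that "we intend to study the combination of all metrics with a linear regression analysis". It mentions no lag, landmark or time-varying term.

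The Background section expects relapse to be common. Problems anticipated foresees people leaving the app: "Patients might dropout by ceasing to share EHR data, by terminating their use of the app, or by becoming unresponsive to follow-ups".

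**The concern.** An exposure that explains an outcome has to come before it. Here the denominator is all messages sent to the user, and nothing stops the count at relapse, so part of the exposure may build up after the outcome has occurred. Someone who has gone back to smoking has less reason to open an app about staying smoke-free. Low engagement can therefore be a result of relapse. Rolling retention and return rate are the most exposed, because they record leaving directly.

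What is at stake is the interpretation of the first secondary objective and of the regression on all metrics. An association produced this way would be reported under a label that attributes it to the system. Randomisation gives no protection, because engagement is not randomised. In the clinical pilot only the app arm, 50 patients, has engagement data at all.

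**Working it through.** The plan states no figure for this association, so there is none to reproduce. Two checks were made, both assuming that reading messages has no effect on relapse.

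**1. Arithmetic on the read ratio**

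Assumptions, none from the documents: messages are sent evenly over 180 days, every user reads 80% of them while abstinent, and a share q after relapsing on day d.

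Ratio for a relapser = (0.8 × d + q × (180 − d)) / 180. An abstainer scores 0.80. The gap is (0.8 − q) × (180 − d) / 180.

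| Relapse day d | q | Ratio | Gap |
|---|---|---|---|
| any | 0.8 | 0.80 | 0 |
| 30 | 0.2 | (24 + 30)/180 = 0.30 | 0.50 |
| 60 | 0.2 | (48 + 24)/180 = 0.40 | 0.40 |
| 30 | 0.6 | (24 + 90)/180 = 0.63 | 0.17 |
| 60 | 0.6 | (48 + 72)/180 = 0.67 | 0.13 |
| 120 | 0.6 | (96 + 36)/180 = 0.73 | 0.07 |
| 150 | 0.6 | (120 + 18)/180 = 0.77 | 0.03 |

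The gap shrinks with later relapse and vanishes if reading does not fall.

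**2. Simulation of the test**

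From the protocol: group sizes, two-sided 0.05, and expected cessation of 0.07 and 0.14 (public) and 0.5 (higher clinical group). The public pilot as a whole was run at 10.5%, the midpoint of 0.07 and 0.14.

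Assumed: one message a day, exponential relapse times, and a personal reading probability averaging 0.60 that is unrelated to relapse and is multiplied by k after relapse. Engagement was split at its median and tested by chi-square, with 1000 runs per row.

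| Setting | k | Abstinent, high vs low engagement | Test rejects |
|---|---|---|---|
| Public, N = 1000, 10.5% | 1 | 10.5% vs 10.5% | 4.2% |
| | 0.9 | 12.1% vs 9.0% | 35% |
| | 0.75 | 14.3% vs 6.8% | 97.5% |
| | 0.5 | 17.7% vs 3.5% | 100% |
| Public intervention arm, N = 500, 14% | 0.75 | 18.8% vs 9.4% | 86.5% |
| | 0.5 | 23.3% vs 5.0% | 100% |
| Clinical app arm, N = 50, 50% | 0.75 | 58.8% vs 40.9% | 29% |
| | 0.5 | 68.7% vs 31.9% | 79% |

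In the public pilot at k = 0.75, the contrast of 14.3% vs 6.8% arises with no effect of reading. It is about as large as the treatment effect the trial is planned to detect, 14% vs 7%.

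**3. Does a landmark remove it?**

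In the same simulation, engagement over days 1 to 14 among users still abstinent at day 14 was tested against abstinence at day 180. Rejection was 4.3% to 6.3% in all scenarios, near the nominal 5%. Day 60 was not simulated, but the principle is the same.

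**4. Who remains at the landmark**

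Under exponential relapse to 10.5% at day 180, the share still abstinent is 0.105^(60/180) = 0.47 at day 60 and 0.105^(14/180) = 0.84 at day 14. For a clinical app arm at 50%, it is 0.5^(60/180) = 0.79 at day 60, about 40 of 50 patients.

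**The case against.** The best reply is that this rests on silence. Table 2 prints no engagement window, engagement could be computed up to each assessment, and an article commonly leaves such detail to the analysis plan. It is true that the six-month window is inferred. It follows from the total-messages denominator and from the common period of treatment and follow-up. However, the definitions that are printed produce the artefact when followed as written, so the point is about what the article fixes and not only about missing detail.

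A second reply is that the objectives speak of comparing and relating, and that the influence label is a grouping entry which the primary-outcome row also carries. That lowers the weight of the label but does not repair the time order.

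Several stronger readings are tempting, and the documents do not support them:

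- **That a correlation between engagement and abstinence will validate the hypothesis.** The Discussion does list app usage statistics among the validating metrics. The preceding sentence, though, presents higher engagement as an expected effect of the messages, and this can be tested by comparing arms in the public pilot, where both arms have app data.
- **That leaving the app also defines failure in the clinical pilot.** Failure there means not returning for the month-6 consultation (Sample size and power calculations). Problems anticipated lists stopping the app and becoming unresponsive to follow-up as separate events.
- **That the association must be strong and positive.** With no fall in reading there is none. In the public pilot, carrying the last observation forward could classify a silent user as a non-smoker, which would weaken or reverse the artefact. That makes the whole-period association harder to interpret, not safer.

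**Conclusion.** The concern holds for the engagement-cessation comparisons and the combined regression. As defined, these metrics let relapse lower engagement, so an association can appear without any effect of the messages. The gap in the read ratio is 0 with no fall in reading and about 0.03 to 0.50 under the illustrative rates and relapse days. The false-positive rate in the public pilot runs from about nominal at k = 1 to near certainty if reading falls by a quarter or more. These sizes depend on assumed reading behaviour, relapse timing and message frequency, and are illustrations, not predictions.

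A reader might infer that the trial's main result is biased. It is not: the randomised comparison of cessation between arms does not use engagement. The point is a worthwhile improvement to a secondary analysis.

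**What to change.** For the engagement-cessation comparisons and the combined regression:

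1. Measure engagement and app usage only up to a pre-specified landmark counted from the quitting date. Day 60 suits the clinical pilot; in the public pilot an earlier two-weekly report could serve. The Materials section counts the visits from the initial consultation, while Table 2 counts from the quitting date, so the time origin should be stated.
2. Relate that engagement to later smoking status among participants abstinent at the landmark.
3. Report whole-period engagement descriptively only.
4. Call the results associations and not system influence.
5. Base any validation from app usage on the between-arm comparison of engagement in the public pilot.

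This changes the analysis wording and needs no new assessments, provided the stored app records carry dates. The protocol does not say that they do, although session frequency and retention could hardly be computed otherwise. Participants already smoking at the landmark leave this analysis: about 53% of public users at day 60, or 16% at day 14, under the relapse pattern assumed above. A landmark addresses reverse causation but not confounding: more motivated users may both read more and stay abstinent, and the report should say so.

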### Sample size and power calculations

Calculations regarding the needed number of participants to measure the primary outcome – smoking cessation rates – have been done to ensure the statistical significance of the results.

For the clinical pilot, accepting an alpha risk of 0.05 and a beta risk of 0.2 in a two-sided test, 45 subjects will be necessary in both the first group and second groups in order to find a statistically significant proportion difference, which is expected to be 0.2 and 0.5 in the first and second groups, respectively.

For the public pilot, accepting an alpha risk of 0.05 and a beta risk of 0.2 in a two-sided test, 489 subjects are necessary in first group and 489 in the second to find as statistically significant a proportion difference, expected to be of 0.07 in group 1 and 0.14 in group 2.

A dropout rate of 15 and 20% is anticipated for the clinical and public pilot, respectively. Although other studies using computer-tailored interventions have reported higher dropout rates, this study will consider participants who do not return for the consultation at month 6 to be failure cases. Consequently, the anticipated dropout rates include only those who withdraw for reasons other than relapse.

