**Fig. 3 Fig3:**
[figure not shown]
Screenshots of the app (English and Mandarin versions) showing different sections

A nurse will provide patients with instructions for downloading and using the app. Questions related to the patient’s basic demographic information and an extended profile (including social influences, plan of action, skills, attitudes, and self-efficacy with regard to smoking) will be assessed in the app.

The data obtained from the database will be analyzed in a comma-separated value (CSV) format using SPSS software.

Users’ physical activity data will be collected using their mobile phones. The mobile app will use GoogleFit [40] to track daily physical activity. These data will be available to users through the GoogleFit app but not displayed within the 3M4Chan app, as it will be utilized for research purposes only.

Patients will be followed up after 60, 120, and 180 days of their initial consultation with a variance margin of 5 days. In the initial consultation, the patient will be assessed in the smoking cessation unit after they have been referred from either the pneumology unit or another clinical department. Smoking-related symptoms, treatment adherence, daily cigarette use, and possible adverse events will be discussed and exhaled carbon monoxide, urinary cotinine, and other clinical information, such as weight and height, will be assessed. Quality of life (EQ-5D-5 L, IPAQ, and SF-36) questionnaires will also be collected. The patient will be instructed on relaxation techniques and on tips to avoid smoking.

During the second consultation, physicians will gather patient information on smoking-related symptoms, treatment adherence, daily cigarette use, possible adverse events, exhaled carbon monoxide and urinary cotinine levels, and other clinical information. Coaching for relapse prevention will be performed.

At the third consultation, information about smoking-related symptoms, treatment adherence, possible adverse events, exhaled carbon monoxide and urinary cotinine levels, and other clinical information will again be collected. New relaxation techniques will be explained if the previously taught techniques have not been effective. Techniques for relapse prevention will be reviewed. It will also be collected the users’ physical and psychological health state, their exhaled carbon monoxide levels, the results from a urinary cotinine test, and will be asked clinical information such as weight and height.

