At the fourth consultation, physicians will collect information about smoking-related symptoms, treatment adherence, and possible adverse events. Techniques for avoiding the risk of relapse are reinforced. Data about blood pressure, weight, height, and quality of life (using EQ-5D-5 L, IPAQ, and SF-36 questionnaires as well as a questionnaire assessing the satisfaction about the motivational messages received through the 3M4Chan app) will also be collected. All input clinical data will be checked for correctness by two healthcare professionals to ensure quality.

The public pilot will use the same mobile app as the clinical pilot. No additional materials will be used.

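### Carrying the last observation forward sets EQ-5D-5L and SF-36 change to exactly zero for month-6 non-returners and, if they also count as failures, can create a lifestyle-cessation link

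*Protocol article*

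**What the plan says.** All statements are in the protocol article.

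- **Metric.** Table 2 (Measures) defines user lifestyle feedback, clinical pilot only, as "Comparison of changes in user lifestyle (at baseline and after 6 months) through the questionnaires" EQ-5D-5L, IPAQ and SF-36. Its listed comparators are "Smoking cessation rate • Mobile app usage".
- **Collection.** Under Materials, the initial consultation has "Quality of life (EQ-5D-5 L, IPAQ, and SF-36) questionnaires will also be collected". The fourth consultation collects "quality of life (using EQ-5D-5 L, IPAQ, and SF-36 questionnaires as well as a questionnaire" on satisfaction with the messages. The second and third consultations name none of the three instruments. The third records "the users’ physical and psychological health state" but does not say how.
- **Missing data.** Statistical analysis: "Missing data will be calculated with the last observation carried forward". No variable is exempted, and all analyses are by intention to treat.
- **Tests.** The same section treats EQ-5D-5L and SF-36 as numerical (t tests and ANOVA) and IPAQ as categorical (chi-square). It also plans a linear regression that combines all metrics.
- **Non-returners.** Sample size and power calculations considers "participants who do not return for the consultation at month 6 to be failure cases". It anticipates 15% dropout in the clinical pilot and says that this figure leaves out withdrawal because of relapse.

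**The concern.** Carry-forward needs an intermediate observation to do anything other than assume no change. This metric has none: it consists of a starting value and a final value. For anyone who misses the final visit, the rule does not estimate the change but fixes it at zero.

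Two things follow. First, the mean change in EQ-5D-5L and SF-36 is pulled toward zero, and a block of identical values distorts the spread on which the t tests and ANOVA rely. Second, the same missed visit can set both variables in a planned comparison. It sets the lifestyle change to zero and, under the failure rule, sets cessation status to failure. The fixed zeros then sit only among failures. If patients on average do change, quitters and failures will appear to differ even when they changed equally.

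At stake are the planned comparison of lifestyle change with cessation and the combined regression. For IPAQ, part of the evidence on the objective that relates physical activity to cessation is also affected.

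**Working it through.** **Inputs from the protocol.** Quit rates q of 0.2 and 0.5 (clinical pilot, Sample size), which average 0.35 with equal arms; 100 patients in total; dropout 15%. The protocol gives no figure for lifestyle change. The calculation that supplies the quit rates reproduces: 0.2 against 0.5, two-sided 0.05, 80% power and a continuity correction give the stated 45 per arm (39 without the correction).

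**Assumptions.** D, the true mean change, is the same in quitters and returning failures, so there is no real association. The non-return share m is 15% for illustration, and 30% to show the effect of added relapse-related non-return. The standard deviation (SD) of change is 1.

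**Step 1: imputed change.** Carried-forward month-6 value minus baseline = baseline − baseline = 0.

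**Step 2: attenuation and spread.** If non-returners would have changed as returners did, overall mean change becomes D × (1 − m), which is 0.85D at m = 15%. The variance becomes (1 − m) × SD² + m(1 − m) × D². With D = 0 and m = 15%, the SD shrinks to √0.85 = 0.92 of its true value, and the whole reduction falls among those imputed.

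**Step 3: link with cessation under the failure rule.**

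- Quitter mean = D
- Failure mean = D × (1 − q − m)/(1 − q)
- Difference = D × m/(1 − q)

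| q | m = 15% | m = 30% (assumed) |
|---|---|---|
| 0.2 | 0.15/0.80 = 0.19D | 0.30/0.80 = 0.38D |
| 0.35 (arms pooled) | 0.15/0.65 = 0.23D | 0.30/0.65 = 0.46D |
| 0.5 | 0.15/0.50 = 0.30D | 0.30/0.50 = 0.60D |

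In the pooled case at 15%, 15 of 65 failures (23%) carry a fixed zero and no quitter does.

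**Step 4: false-positive rate.** Simulation of a pooled t test of quitters against failures: 100 patients, 35 quitters, no true difference, 10,000 runs, nominal level 5%.

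| D (in SD) | carry-forward, m = 15% | carry-forward, m = 30% |
|---|---|---|
| 0 | 5.8% | 7.7% |
| 0.2 | 6.4% | 10.4% |
| 0.5 | 10.2% | 26.4% |
| 0.8 | 15.4% | 49.4% |

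With observed changes only, rejection was 4.7% to 5.1% in all of these scenarios. The excess at D = 0 reflects unequal spread, since no mean difference exists there.

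**Step 5: if smoking status is carried forward instead.** Let f be the share of non-returners last classed as abstinent, with q now including them. The difference becomes D × m × [(1 − f)/(1 − q) − f/q]. At f = 0 this is Step 3. At q = 0.35, m = 15% and an assumed f of 0.2 it is 0.15 × (1.231 − 0.571) = 0.10D, against 0.23D. It reaches zero at f = q and changes sign beyond that. Step 2 is unchanged.

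**The case against.** The strongest case on the other side has five parts.

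- **The activity objective.** A reader might infer that imputation alone could answer the activity-cessation objective positively. The documents do not support that. IPAQ is tested as categorical, so the mean-change and spread arithmetic does not describe its test. Activity is also measured separately by GoogleFit minutes, which are not a two-visit change score and are not covered by this argument. What stands is that non-returners are recorded as unchanged on IPAQ, so part of that evidence is affected.
- **The scoring of cessation.** A reader might infer that the link arises however smoking status is scored. It does not. It needs the failure rule in the sample size section, and under the carry-forward rule in Statistical analysis it would be weaker (Step 5). Those two rules conflict for a non-returner last classed as abstinent, which is a separate matter. The attenuation stands under either.
- **The 15%.** It excludes withdrawal because of relapse, so it is not the protocol's figure for all non-returners scored as failures. It serves here only as an illustration.
- **Size.** A spurious difference in means requires a non-zero D. The protocol gives neither a mean nor an SD, and at 15% non-return the effect is modest. This stands.
- **The contrast.** Table 2 names the comparison with the cessation rate without saying that quitters and failures will be compared. That grouping is the natural reading, but it is inferred.

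The third consultation might seem to offer an intermediate value, but no instrument is named there, and Table 2 fixes the two time points. The schedule figure is not available to check.

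**Conclusion.** The point holds for EQ-5D-5L and SF-36 change in the clinical pilot. As written, the blanket carry-forward rule gives zero change to every month-6 non-returner with a baseline questionnaire, which attenuates mean change and distorts its spread. For IPAQ the equivalent is a record of no change.

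The artificial link with cessation is conditional on two things: non-returners counted as failures, and a non-zero mean change, whose sign the link follows. Under those conditions it is 0.19D to 0.30D at 15% non-return across the planned quit rates, and 0.38D to 0.60D at an assumed 30%. The matching false-positive rates, with D between 0.2 and 0.8 SD, are about 6% to 15% and 10% to 49%. D, its SD and the true non-return share are assumptions.

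This affects one secondary metric in the smaller pilot. It is still worth correcting, because the rule is fixed in the protocol and the correction is cheap.

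**What to change.** In Statistical analysis, exempt the EQ-5D-5L, SF-36 and IPAQ questionnaires from last observation carried forward, and state that:

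1. Month-6 EQ-5D-5L and SF-36 scores are analysed with adjustment for the baseline score.
2. Missing month-6 scores are multiply imputed from arm, baseline score, available 60- and 120-day CO and cotinine status, and month-6 cessation status as scored in the analysis. Cessation status must be included because it is the variable being compared; leaving it out can bias the association toward zero.
3. Missing 60- and 120-day results are imputed jointly, since patients lost early will lack them too.
4. IPAQ is imputed with a categorical model, to match its planned chi-square test.
5. Baseline carried forward is reported only as a sensitivity analysis.

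The cost is a change of analysis wording and some extra programming; no new data collection is needed. The drawbacks are reliance on data being missing at random given these predictors, and a somewhat wider interval.

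### Physical activity is an undivided total of minutes per user, so it mixes how long a user was tracked with how active the user was

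*Protocol article*

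**What the plan says.** The Calculation column of Table 2 (Measures: baseline and outcome and process measures) defines physical activity as "Total time (min) of activity per user, retrieved by GoogleFit". The Comparisons column of that row lists "Smoking cessation rate • Mobile app usage". The row serves the third secondary objective (Design and setting), which asks about a relation between users' "physical activity levels and their mobile app usage, and their smoking cessation rates".

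On data capture, Materials says: "The mobile app will use GoogleFit [40] to track daily physical activity". Under Statistical analysis, physical activity is a numerical variable assessed with t tests and ANOVA. A linear regression combining all metrics is also planned, and last observation carried forward (LOCF) is the only missing-data rule.

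On length of observation, participants in both pilots are to be "treated and followed up for 6 months". However, Problems anticipated expects some to drop out "by terminating their use of the app, or by becoming unresponsive to follow-ups". Sample size and power calculations adds: "A dropout rate of 15 and 20% is anticipated for the clinical and public pilot, respectively". That section explains that these rates leave out withdrawal because of relapse, and that a participant who does not come back at month 6 counts as a failure.

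**The concern.** The objective is about activity levels, but the stated calculation is a sum. A sum of daily minutes equals the daily level multiplied by the number of days counted. It measures level only if everyone is counted over the same number of days, and the protocol's own dropout figures make that unlikely.

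The planned comparisons are exposed because their other side also depends on staying. A participant who leaves before month 6 can have both a truncated activity total and a failure on cessation. App usage has no row under that name in Table 2. The nearest row, time spent per app section, is again an amount with no stated time base, so it too would tend to grow with time in the study. A positive association could then be reported as a finding on activity when it reflects retention.

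Table 2 does divide by exposure elsewhere: individual engagement is messages read over messages sent.

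**Working it through.** The protocol gives no figure for physical activity, so there is none to reproduce. The check asks what the stated formula returns when daily activity is the same for everyone.

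**Inputs from the protocol article.** Follow-up of 180 days; dropout of 15% and 20%; 500 users per public arm; expected cessation in the second group of 0.14 (public) and 0.5 (clinical); two-sided tests at 0.05.

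**Assumptions, not in the protocol.** Daily activity has mean 30 min (20 to 60 shown) and SD 15 min. Tracking ends when a user leaves. Leavers' tracked days are uniform on 1 to 180, and stayers have 180.

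**1. Formula.** Total = minutes per day × days tracked.

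| Min/day | 60 days | 180 days | Ratio |
|---|---|---|---|
| 20 | 1200 | 3600 | 3.0 |
| 30 | 1800 | 5400 | 3.0 |
| 60 | 3600 | 10800 | 3.0 |

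The ratio is 180/60 at any daily rate. It illustrates one pair of durations and is not an expected effect.

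**2. Stayers against leavers.** Mean tracked days of leavers = (1 + 180)/2 = 90.5. Mean total = 30 × 90.5 = 2715 min, against 30 × 180 = 5400 min for stayers: a ratio of 5400/2715 ≈ 2.0. A simulation of 1000 users with 20% leaving agrees (about 2713 and 5400 min). With no true difference, a t test on totals rejected in 100% of runs. The correlation of the total with days tracked was about 0.45.

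**3. Quitters against failures.** Failures also include users who stay and relapse, so the contrast in Table 2's cessation comparison is smaller than in step 2. Suppose all leavers are failures and all quitters are tracked for 180 days.

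- Public, 14% quit and 20% leave: the 86% failures are 20 points leavers and 66 points stayers. Mean days = (20 × 90.5 + 66 × 180)/86 = 159.2; ratio 180/159.2 ≈ 1.13.
- Clinical, 50% quit and 15% leave: mean days of failures = (15 × 90.5 + 35 × 180)/50 = 153.2; ratio ≈ 1.18.

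Relapse-related withdrawal comes on top of these dropout rates. If 50% of public users left in all (assumed), mean days of failures would be (50 × 90.5 + 36 × 180)/86 = 128.0, a ratio of about 1.41.

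**4. Between public arms of 500, equal daily activity (simulated).**

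| Leaving, arm A / arm B | False rejection, total | False rejection, per day |
|---|---|---|
| 20% / 20% | about 6% | about 5% |
| 30% / 20% | about 32% | about 5% |
| 40% / 20% | about 85% | about 5% |

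The unequal rates are assumptions; the protocol states none by arm.

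**5. After the change.** With minutes per tracked day, stayers and leavers both average about 30 min, the correlation with days tracked is about 0.00, and the t test of step 2 rejects in about 6% of runs.

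**The case against.** The strongest reply is that the table cell names no window. With daily tracking, a total per day or per follow-up interval would also fit, and a condensed article may leave this to a fuller document. That has some force, but the column states a calculation, and the plain reading of a total per user is a sum over the user's time in the study. An analysis plan that followed it would inherit the problem.

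A reader might infer that relapse itself ends tracking, or that GoogleFit retrieval certainly stops when a user stops opening the trial app. The protocol says neither. It records repeated quit attempts, so users can continue after a failed one, and GoogleFit is a separate app that could keep recording. Because the trial app does the tracking and nothing says data would be retrieved after a user leaves, fewer tracked days is the probable result for leavers, but not a certain one. Likewise, the 20% is trial dropout, not a measured loss of tracking days, and someone who only stops sharing health-record data may still be tracked.

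The month-6 failure rule is worded as non-return for a consultation, which the public pilot does not have. If public leavers were instead carried forward as non-smokers under LOCF, the link with cessation would be weaker there; the link with app usage would remain.

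Two possible remedies within the plan fall short. LOCF applied to a cumulative total leaves it at its truncated value. The IPAQ, collected at baseline and 6 months, does not depend on days tracked, but it is used only in the clinical pilot.

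**Conclusion.** The point holds as a flaw in the stated calculation. Followed as written, it confounds activity level with length of tracking, and the third secondary objective cannot separate the two.

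The size rests on assumed leaving times and on tracking ending with departure. Stayers would have about 2 times the leavers' total. Quitters would have roughly 1.1 to 1.4 times the total of failures in the public pilot (20% to 50% leaving) and about 1.2 times in the clinical pilot. The threefold ratio applies only to 180 against 60 days.

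It would be tempting to conclude that the comparison of randomised arms is biased too. That needs tracked time to differ between arms, and with 20% leaving both arms the test keeps close to its nominal level. In the clinical pilot the question does not arise, because Table 1 lists physical activity only for the intervention arm.

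This is a secondary metric. The primary outcome and the sample size are not affected. The change should be made but is not critical.

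**What to change.** In Table 2, replace the total with mean minutes per day over the days on which the app was connected to GoogleFit, counting connected days with zero activity as zero. Dividing only by days with recorded activity would inflate the mean for sporadic users. Alternatively, use the mean over a common fixed window. In either case:

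- set a minimum number of tracked days in advance;
- state how a day without a connection is told apart from a day without activity;
- use the same measure in every Table 2 comparison and in the regression;
- report days tracked separately, by arm and by cessation status.

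Activity is already tracked daily, so no new activity data are needed. The cost is a revised table entry with these short rules, and the loss of users with too few tracked days. The change removes the built-in dependence on days tracked. It does not remove selective dropout: if those who leave differ in daily activity from those who stay, or change their activity after leaving, that remains, and the reported days tracked would help readers judge it.
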